**Methods:**

This trial is a 2-arm, unblinded, parallel, pragmatic randomized controlled trial with a qualitative component. Eligible participants will be women who live in the Maritime provinces of Canada (New Brunswick, Nova Scotia, and Prince Edward Island), who are in midlife and older (aged approximately ≥50 years), and who are currently in a relationship with an abusive partner or have recently left an abusive partner. Facilitators will be trained to deliver the intervention. The intervention will be entirely virtual and will consist of 2 components: (1) an empowerment component, which will involve sharing resources and information with the women; and (2) a social support component, which will include providing support and encouragement to women for 12 weeks. Quantitative effectiveness data will be collected from all trial participants at baseline, 3 months after the intervention, and 9 months after the intervention about the incidence and severity of IPV, physical and mental health, and safety behaviors and strategies. Qualitative interviews will be conducted with the facilitators and intervention group participants. Control group participants will receive a static, nontailored version of the advocacy intervention for midlife and older women (AIM) intervention materials after baseline data collection.

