### Eligibility Criteria

The following inclusion criteria will be used to determine if women are eligible to be enrolled in the trial. The potential participants are those who self-identify as a woman; are in midlife and older (aged approximately ≥50 years); are currently living in the Maritime provinces; can participate in an interview in either English or French; and are currently in a relationship with an abusive partner or have recently left an abusive partner within the last year, including a same-sex partner.

In a recent systematic review [27], our team used the theoretical concepts of reclaiming self-theory and the four levels of prevention [28-31] to classify IPV interventions into the categories of (1) preventing IPV, (2) identifying and documenting IPV, (3) supporting women while living with or leaving an abusive partner, and (4) supporting women after leaving an abusive partner. The intervention used in this trial will target women in category 3 as it is designed to empower women to make decisions and take action related to the abuse they are experiencing or have recently experienced.

The dynamics of abusive relationships are such that leaving an abusive partner is often a process that involves leaving and returning multiple times [32]. During this process, the woman may reach out to available services, such as outreach services, or live in a transition house or other form of safe housing. Thus, the participants may have already contacted IPV services and may be using various forms of services or initiatives during the course of this study. Given that our research team will not be interfering with the supports and services that the participants are already using during their participation in the study, this study aligns with the tenets of a pragmatic trial [33]. Our team has had success recruiting older women experiencing IPV who had already accessed services, but we have had challenges recruiting older women in the region who have never contacted an organization for support [14]. The intervention is designed to provide information about other resources and supports available to women and to encourage women to use these services; therefore, it is not a concern that the women access and use other supports during our study.

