### Outcomes Measured

Research staff will collect quantitative effectiveness data from participants by telephone or video call at 3 time points: baseline, 3 months, and 9 months. Research staff will schedule a meeting by telephone or Zoom (Zoom Video Communications) to collect the survey responses from participants verbally. Table 1 details the survey information to be collected directly from participants.

**Table 1 table1:** Quantitative measures.

Quantitative measure collected	Time point for data collection			Explanation
	Baseline	3 months	9 months	
Screening questions	✓			Age, province of residence, and description of the stage of their relationship with their abusive partner
Demographic information	✓			Education, marital status, and diversity characteristics (eg, immigrant status, francophone status, ethnic status, and rural status)
WEB^a^	✓	✓	✓	To measure women’s experiences of feeling fearful and controlled by their abusive partner [43]
DCS^b^	✓	✓	✓	To measure the conflict (ie, difficulty) that women endure in making decisions about leaving their abusive relationship [44]
IPV^c^ strategies index	✓	✓	✓	To measure the different types of IPV strategies that women are using to keep themselves safe in their abusive relationship [45]
SF-12v2^d^	✓	✓	✓	To measure quality of life [46]
CES-D^e^	✓	✓	✓	To measure depressive symptoms [47]
ISEL^f^	✓	✓	✓	To measure perceived social support [48]

^a^WEB: Women’s Experiences of Battery Scale.

^b^DCS: Decisional Conflict Scale.

^c^IPV: intimate partner violence.

^d^SF-12v2: Short Form Health Survey.

^e^CES-D: The Center for Epidemiologic Studies Depression Scale.

^f^ISEL: The Interpersonal Support Evaluation List.

Primary outcomes include (1) physical and mental health, (2) knowledge about IPV, and (3) safety strategies. Physical and mental health will be assessed using the following scales: Short Form Health Survey [46], Centre for Epidemiologic Studies Depression Scale [47], and Interpersonal Support Evaluation List [48]. Knowledge about IPV and safety strategies will be measured using the following scales: the Women’s Experiences of Battery Scale [43], Decisional Conflict Scale [44], and Intimate Partner Violence Strategies Index [45].

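### Knowledge about IPV is one of three primary outcomes, but none of the six scales is described as measuring it

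*Protocol article*

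**What the plan says.** Under Outcomes Measured, the protocol article states: "Primary outcomes include (1) physical and mental health, (2) knowledge about IPV, and (3) safety strategies". It gives the SF-12v2, CES-D and ISEL to the first domain. For the other two it says: "Knowledge about IPV and safety strategies will be measured using the following scales", and lists the WEB, the DCS and the IPV Strategies Index jointly, without saying which scale serves which domain.

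Table 1, in the same section, gives each scale's purpose. The WEB is there "To measure women’s experiences of feeling fearful and controlled by their abusive partner". The DCS captures the "conflict (ie, difficulty) that women endure in making decisions about leaving their abusive relationship". The Strategies Index records what women do to stay safe within the relationship.

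The Methods paragraph of the abstract describes the effectiveness data as being "about the incidence and severity of IPV, physical and mental health, and safety behaviors and strategies". Knowledge is not in that list. The Discussion (Anticipated Principal Findings) nevertheless expects a benefit on all three primary domains, knowledge included, and expects that controls may also gain in knowledge, but less.

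Eligibility Criteria admits women who "are currently in a relationship with an abusive partner or have recently left an abusive partner within the last year".

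**The concern.** A primary outcome needs an instrument that measures it. Here the article itself assigns scales to the knowledge domain, and its own table says that those scales measure something else. If the plan is followed as written, a fall in fear, or less difficulty in deciding about leaving, would be reported as women knowing more about IPV. A woman can know a great deal about abuse and remain afraid; she can also become less afraid without learning anything. The label on one of the three headline results would not match the data behind it.

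The abstract adds to this, because it names a different set of measured domains from the Methods. A reader comparing the final report with the protocol could not tell which outcomes had been promised.

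**Working it through.** No figure in the plan needs to be reproduced for this point. The check sets each scale's stated purpose in Table 1 beside the outcomes named in the text.

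**Step 1: scale by scale, does Table 1 describe a measure of knowledge?**

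- WEB: fear of, and control by, the partner. No.
- DCS: difficulty in decisions about leaving. No.
- IPV Strategies Index: safety strategies in use, which is behaviour. No.
- SF-12v2: quality of life. No.
- CES-D: depressive symptoms. No.
- ISEL: perceived social support. No.

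Count: 0 of 6.

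**Step 2: which primary outcomes have an instrument?**

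- Physical and mental health: yes (SF-12v2, CES-D, ISEL).
- Safety strategies: yes (IPV Strategies Index).
- Knowledge about IPV: none.

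Count: 1 of 3 without a matching measure. The WEB and the DCS are left without an outcome named for what they measure.

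**Step 3: abstract against Table 1.** The abstract promises incidence and severity of abuse. No scale in Table 1 is described as counting abusive acts, so incidence has no measure. Severity is less clear-cut, since the WEB may bear on severity as the woman experiences it. Knowledge is primary in the Methods and absent from the abstract's list.

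**Step 4: scale wording against eligibility.** Women who left within the last year can enrol. Table 1 describes the DCS by reference to "endure in making decisions about leaving their abusive relationship", and the Strategies Index by reference to safety inside the relationship. Both descriptions presuppose a relationship that continues. The WEB's description, "experiences of feeling fearful and controlled by their abusive partner", fits a former partner equally well. So two scales are affected, the DCS and the Strategies Index. Relationship stage is among the screening questions in Table 1, so the variable needed to look at this is already collected.

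**The case against.** **The match is judged on one-line summaries.** The items of the WEB, the DCS and the Strategies Index are not shown, and some could touch on knowledge. This caveat stands. Still, the article chose those summaries to say what each scale is for, and none mentions knowledge.

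**The text could mean knowledge of both IPV and safety strategies as a single domain.** This reading is weak, because the list of primary outcomes numbers the two separately.

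**Much of the trial is unaffected.** This stands. A reader might infer that the trial cannot reach its conclusion at all. The documents do not support that: two of the three domains have scales, and the article's Conclusions section claims only preliminary evidence of effectiveness, without mentioning knowledge.

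**Women who have left may still face the decision.** This also stands in part. Eligibility Criteria says that leaving is often a process with several returns, so the DCS may still apply to some women who have left. A reader might infer that the DCS is meaningless for them, that the WEB has the same problem, or that the effect is diluted by a calculable amount. None of these is supported. The WEB's description is not tied to a current partner. The article gives no share of women who have left, and it states no effect size, alpha or power from which a loss could be computed. What remains is that the article does not say how these women's answers on the two scales are to be read.

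**Conclusion.** The point holds for the knowledge outcome, and there it is wrong as written. By the article's own descriptions, 0 of 6 scales measures knowledge and 1 of 3 primary outcomes has no matching measure. The listed data can show neither the knowledge benefit that the Discussion anticipates nor the smaller gain it expects in controls. The mismatch is not a detail left to a fuller document, because the article states the mapping explicitly and its own table contradicts it.

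The abstract's wording is a lesser inconsistency: incidence of abuse is promised without a measure of it, and knowledge is not listed.

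The fit of the DCS and the Strategies Index to women who have left is a secondary point about interpretation. Its size cannot be given from the documents. The whole conclusion rests on Table 1's descriptions, since the item wording is not shown.

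**What to change.** By a recorded and dated amendment before analysis:

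1. Map each scale to one outcome named for what it measures: WEB to fear and control, DCS to decisional conflict, IPV Strategies Index to safety strategies. Keep the three health scales as they are assigned.
2. Withdraw knowledge about IPV as a primary outcome under Outcomes Measured, and as an anticipated finding in the Discussion.
3. Align the abstract's list of data with Table 1, so that incidence of abuse is not promised without a measure.
4. As a supporting analysis, report the DCS and the Strategies Index by the relationship stage recorded at screening.

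The cost is mainly that the trial claims less. Because recruitment began in October 2023 (Participant Involvement by Group), withdrawing a primary outcome is a change during the trial and needs a stated reason. Adding a knowledge scale instead would leave women already enrolled without a baseline value, so renaming is the more practical route.

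The breakdown by stage needs no new data. It will be imprecise with the planned 30 women per arm, and baseline stage does not capture women who leave or return during follow-up. It should therefore support the full comparison and not replace it.

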#### Components of AIM

The empowerment component is derived from the empowerment model by Dutton [37] to increase women’s safety. This component will involve the facilitator providing a 1-hour-long individual one-on-one information-sharing session with the participants that will be delivered virtually by telephone or video call. These sessions will include providing information on recognizing increased danger and how to use an individualized safety plan adapted for older women, providing information about cycles of violence, providing community and legal resources, and developing goals and strategies for the future. In addition to discussing this information, print materials will be provided electronically (via email) or in hard copy (via postal mail). Thus, this component clearly contributes to awareness raising and also empowers the women to develop changes in the future.

The social support component is based on the social support theory by Cohen [38] that involves tangible and perceived social support to contribute to health and well-being. This component will involve the facilitator scheduling weekly telephone or video calls over a course of 12 weeks at a time that is convenient to the participant. The duration of calls is variable and would average approximately 20 minutes per call. The calls are intended to provide encouragement and support and to answer questions the participant may have about using or applying the resources provided in the empowerment component. There are no specific or scheduled topics that are planned for each session. These are very individualized and based on the women’s needs and questions that each woman may wish to discuss. For example, facilitators will be prepared to help women with recognizing their past abuse and processing the abuse as well as providing support to women who are undergoing court proceedings and legal issues. The social support provided through the weekly contact is a key component of the intervention in addition to the topics discussed.

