## Discussion

### Anticipated Principal Findings

We anticipate that the quantitative data will reveal positive outcomes for participants in the intervention arm on our primary outcome measures of (1) physical and mental health, (2) knowledge about IPV, and (3) safety strategies. Given that the participants in the control arm will receive a static, nontailored version of the AIM intervention materials after baseline data collection, we expect that there could be some positive outcomes on items such as knowledge about IPV and safety strategies but to a lesser extent than for the participants in the intervention arm.

We anticipate that the qualitative data will reveal the value of offering the AIM intervention to midlife and older women who have experienced IPV. We expect that the qualitative findings will reveal how the content and delivery of the program can be improved for both the participants and the facilitators.

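### Knowledge about IPV is a primary outcome, but the protocol's own table describes none of the scales assigned to it as measuring knowledge

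*Protocol article*

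**What the plan says.** Under Outcomes Measured, the protocol article lists its primary outcomes: "Primary outcomes include (1) physical and mental health, (2) knowledge about IPV, and (3) safety strategies". It assigns the SF-12v2, the CES-D and the Interpersonal Support Evaluation List to the first. The second and third are taken together: "Knowledge about IPV and safety strategies will be measured using the following scales", followed by the WEB, the DCS and the IPV Strategies Index.

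Table 1 in the same section gives each scale a one-line purpose. For the WEB it is "To measure women’s experiences of feeling fearful and controlled by their abusive partner". For the DCS it is "To measure the conflict (ie, difficulty) that women endure in making decisions about leaving their abusive relationship". The Strategies Index is described as recording the kinds of strategy a woman uses to stay safe.

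The Discussion (Anticipated Principal Findings) forecasts benefit for the intervention arm on "our primary outcome measures of (1) physical and mental health, (2) knowledge about IPV, and (3) safety strategies". It adds that the comparison arm may also gain on knowledge and safety strategies, though less.

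**The concern.** A primary outcome needs an instrument that measures the construct it names. Here the outcome list promises a result on knowledge, while the table in the same section says the assigned scales capture an experience, a decision state and a behaviour. If the assignment is followed, lower fear and control, or lower decisional conflict, would count towards a conclusion about what women know.

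That matters because a between-arm difference in knowledge is predicted. Both arms receive an information package, in the comparison arm a condensed, untailored one, so whether AIM adds knowledge beyond the package is a real question that needs a measure of knowledge. The Dissemination section also ties public release of the programme to AIM being found effective, and a knowledge claim resting on other constructs could feed that judgement.

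**Working it through.** The plan gives no figure on this point to reproduce. The check sets the outcome list against the instrument list.

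**Inputs.** The three primary outcomes and their scale assignments come from the text of Outcomes Measured. The scale descriptions come from Table 1 in that section, which is introduced as setting out the survey information taken directly from participants. Table 1 has eight rows: two collected at baseline only, and six scales collected at baseline, 3 months and 9 months.

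**Match of repeated scales to outcomes.**

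| Scale | Primary outcome it is assigned to | Construct in Table 1 (paraphrased) | Described as knowledge? |
|---|---|---|---|
| SF-12v2 | Physical and mental health | Quality of life | No |
| CES-D | Physical and mental health | Depressive symptoms | No |
| ISEL | Physical and mental health | Perceived social support | No |
| WEB | Knowledge / safety strategies | Fear of and control by the partner | No |
| DCS | Knowledge / safety strategies | Difficulty in deciding about leaving | No |
| IPV Strategies Index | Knowledge / safety strategies | Safety strategies in use | No |

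**Counts.**
- Scales described as measuring knowledge: 0 of the 6 repeated, and 0 of the 3 assigned to it.
- Assigned scales whose description fits either knowledge or safety strategies: 1 of 3, the Strategies Index, which fits safety strategies.
- Primary outcomes with no scale described as measuring them: 1 of 3.

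**Baseline-only rows.** These cover screening items (age, province, relationship stage) and demographics. Neither holds a knowledge item.

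**Alternative parsing.** The assignment sentence could be read as knowledge of two things, IPV and safety strategies. This does not help. The outcome list numbers them as separate outcomes, and no scale is described as measuring knowledge of either. The Strategies Index is described as recording use.

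**Cross-check with the Abstract.** Its Methods paragraph lists the effectiveness data as incidence and severity of IPV, health, and safety behaviours and strategies. Knowledge is not in that list.

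**The case against.** The strongest reply has four parts.

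1. **Table 1 gives one line per scale.** Item content lies in cited sources that are not available here, so some items may touch on what a woman knows. This stands to the extent that the supportable statement is that no scale is described as measuring knowledge. A reader might infer that the trial will hold no data at all bearing on knowledge; the documents do not establish that.

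2. **Scoring and scale-by-scale mapping are commonly left to an analysis plan or full protocol.** This is true, and the lack of such detail is not the point. The article does state an assignment, and its own table contradicts it. An analysis plan could set scoring, but could not turn these scales, as described, into knowledge measures.

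3. **Nothing formal hangs on the knowledge domain.** The Sample Size and Statistical Analysis sections attach no decision rule, sample size or test to it, and the article calls its evidence provisional and preliminary. This limits the consequence to interpretation. Knowledge nonetheless remains a named primary outcome with a predicted result.

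4. **The direction of the WEB.** Because the article says of the empowerment component that "this component clearly contributes to awareness raising", and facilitators may help women recognise past abuse, a reader might infer that a higher WEB score could be presented as better knowledge, so that a worsening passes as a gain. The documents do not support this. Those statements describe intervention content and are not linked to WEB scoring. No section treats a higher score as benefit, fear and control have an evident adverse end, and scoring direction is commonly left to the analysis plan. This inference forms no part of the finding.

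**Conclusion.** The concern holds as a contradiction within Outcomes Measured. One of the three primary outcomes is assigned to scales that Table 1 describes as measuring other things, and none of the six repeated scales is described as measuring knowledge. The knowledge gain forecast in the Discussion therefore could not be supported by the measures as described.

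This rests on two assumptions: that Table 1 is the complete list of survey measures, as its introduction indicates, and that its descriptions are fair to the scales. No estimate, test or sample size is affected. What changes is what the trial may conclude from the WEB and the DCS.

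**What to change.** Amend the protocol, with a date and a reason, before any between-arm results are examined:

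- Remove knowledge about IPV from the primary outcomes under Outcomes Measured and from Anticipated Principal Findings.
- Name the WEB outcome as fear of and control by the partner, and the DCS outcome as decisional conflict, following Table 1.
- Keep the Strategies Index as the safety-strategies outcome.
- State that no conclusion about knowledge will be drawn from these scales.

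Timing matters because recruitment has begun and the Results section says that analysis runs throughout data collection.

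Adding a few knowledge questions at follow-up would not be a sound repair. They would have no baseline. The arms would also answer them on different clocks, since Participant Involvement by Group times follow-up from the final support session in the AIM arm and from the baseline surveys in the comparison arm.

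The cost is a documented mid-trial outcome change, with whatever ethics notification that requires, and the loss of the knowledge claim. No participants, visits, data items or tests are added.
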